## **Randomisation**

Participants will be randomized 1:1 to the PCI performed using standard care or technology-assisted PCI in blocks to ensure balanced distribution of the treatment groups at all times. The study team will enter the participant screening information into the electronic data capture (EDC) system after informed consent has been obtained. Once the participant is determined to be eligible prior to the Index Procedure the study team will randomise the participant using the EDC. The Investigator will be advised of this and the allocated method of PCI will be performed. The participant will ideally remain blinded to the method of PCI performed.

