## **Index Procedure (PCI)**

Participants who meet the eligibility criteria will be randomized within 24 hours prior to their PCI.

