### Data to be collected prior to initiating PCI

- Operator and assistant details
- Arterial access site and side
- Procedure start time (Sheath insertion)
- PCI Start Time (Guide Catheter Insertion)
- American Heart Association/American College of Cardiology lesion classification

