### Data to be collected during the procedure

- Guidewire activation to guidewire retraction
- Fluoroscopy time
- Participant and staff radiation exposure (dose area product (DAP) and air kerma (AK))
- Lesion characteristics (eg tortuosity, calcification and bifurcation)
- Operator assessment of stent length
- Robotic assessment of stent length
- Contrast volume
- Procedure end time (Guide Catheter out)
- Equipment utilisation
- Pre and post PCI stenosis percentage
- Need for manual input (if required) and reason for this
- Number of times stent visualisation technique (eg stent boost or clearstent) used
- Use of robotic algorithms (techIQ) to assist lesion navigation
- Any adverse events
- Use of intracoronary physiology and/or intracoronary imaging
- Operator survey of task load

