# Data Management, Statistical Analysis and Record Keeping

## **Statistical Methods**

This is a double-arm, open-label, randomized controlled trial of the CorPath GRX System designed to evaluate the safety and effectiveness of the clinical and technical performance of the CorPath GRX System in the delivery and manipulation of coronary guidewires and stent/balloon catheters, and remote manipulation of guide catheters for use in PCI in comparison to standard of care. The analysis of data collected as part of the RCT will include, but may not be limited to, the Objectives and Measures outlined in Section 3.0 of this protocol. Continuous variables will be summarized using the number of observations, mean, standard deviation, median, min and max values. Categorical variables will be summarized with the number and percent in each category out of the number observed. Two-sided 95% confidence intervals may be calculated and two-sided p-values < 0.05 will be considered statistically significant.

The outcome of patient radiation exposure will be analysed using variance (ANOVA). As each participant may have multiple lesions, the outcome of clinical success at day 3 will be analysed using a two level multilevel models. Logit link will be used with a binomial distribution and restricted maximum likelihood (REML) will be used for estimation. Predictor variables in the models will include treatment group.

Technical success will analysed with Fisher’s exact test, comparing the proportion of participants with technical success between the two groups. Logistic regression will be used to compare technical success accounting for lesion complexity. For all other secondary outcomes, continuous outcomes will be measured using independent t-test (or non-parametric alternative depending on distributional assumptions), and categorical outcomes analysed by Fisher’s exact test. For outcomes measured repeatedly over time, multilevel models with an appropriate link functions will be used for analysis.

All statistical analyses will be performed using SAS software (version 9.4) or other widely accepted statistical or graphical software.

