**ACC/AHA Lesion Characteristics (Type A, B and C):**

- *Type A Lesions (high success, >85%; low risk)*: Discrete (<10mm length), concentric, readily accessible, nonangulated segment ,45^o^, smooth contour, little or no calcification, less than totally occlusive, non-ostial in location, no major branch involvement and absence of thrombus.
- *Type B (B1 and B2) Lesions (moderate success, 60 - 85%; moderate risk)*: Tubular (10-20 mm length), eccentric, moderate tortuosity of proximal segment, moderately angulated, 45 - 90^o^ , irregular contour, moderate or heavy calcification, ostial in location, bifurcation lesions requiring double guidewires, some thrombus present and total occlusion < 3 months old. Type B2 lesion classification has more than one characteristic above.
- *Type C Lesions (low success, < 60%; high risk)*: Diffuse (>2 cm length), excessive tortuosity of proximal segment, extremely angulated, > 90^o^, inability to protect major side branch, degenerated vein grafts with friable lesions and total occlusions > 3 months old.

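### Technical success is adjusted for a lesion complexity grade that, as scheduled, is recorded after the allocation is known, so the adjusted odds ratio can be biased towards the device

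*Protocol*

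**What the plan says.** All references are to the protocol.

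- **Analysis (8.1).** Technical success is first tested by Fisher's exact test, "comparing the proportion of participants with technical success between the two groups". Then: "Logistic regression will be used to compare technical success accounting for lesion complexity". No field is named as the complexity variable.
- **Timing of allocation (7.2).** "Participants who meet the eligibility criteria will be randomized within 24 hours prior to their PCI".
- **Disclosure (5.3).** Once the EDC has randomised the participant: "The Investigator will be advised of this and the allocated method of PCI will be performed". Only the participant is, ideally, blinded. Section 8.1 opens with "This is a double-arm, open-label, randomized controlled trial of the CorPath GRX System".
- **Complexity field 1 (7.2.2).** "American Heart Association/American College of Cardiology lesion classification" is listed with the sheath and guide catheter insertion times, as data to be collected before the PCI is initiated.
- **Complexity field 2 (7.2.3).** "Lesion characteristics (eg tortuosity, calcification and bifurcation") is listed as data to be collected during the procedure.
- **Overlap (Appendix A).** The AHA/ACC class is built partly from the same features; type B, for example, includes "moderate tortuosity of proximal segment".
- **Schedule (3.3).** Lesion assessment appears only in the index procedure column, not at screening.
- **Independent review (10.2).** The events committee reviews clinical events. No independent or blinded grading of lesions is mentioned.

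**The concern.** A covariate in a randomised comparison should be something the assigned arm cannot influence. Lesion complexity meets that requirement if it is graded before allocation, or by a reader who does not know the arm. Here it is graded afterwards, at a procedure where the arm is known.

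There are two routes to bias:

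1. **Arm-aware grading.** Whoever grades a lesion about to be treated robotically may grade it as more complex than the same lesion about to be treated manually. Lesions in the robotic complex stratum are then easier on average than those in the manual one, and the model credits the device for handling difficult anatomy. This can happen even if every field is entered on time.
2. **Outcome-aware grading.** If the 7.2.3 fields are used, or the class is completed late, a lesion the robot failed to treat may be recorded as more tortuous or calcified. Part of the device failure then passes into the covariate.

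At stake is the adjusted comparison of technical success, a main effectiveness measure of the trial. An analysis plan can name the variable, but it cannot turn a grade given with the arm known into a pre-allocation one.

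**Working it through.** **Step 1: order of events.** Reading 5.3, 7.2, 7.2.2 and 7.2.3 together gives: eligibility confirmed; randomisation within the day before PCI; investigator told the arm; sheath and guide catheter inserted and AHA/ACC class entered; procedure performed and the remaining lesion characteristics entered. Both complexity fields come after disclosure.

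**Step 2: the plan's own figures.** The only design figure is the power for patient radiation exposure. It reproduces: the difference is 0.20 × 1284 = 256.8 mGy, the pooled SD is √((180² + 142.83²)/2) = 162.48, and 150 per arm gives power above 99% (15 per arm would already give 99%). It has no bearing on technical success, for which the protocol gives no rate.

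**Step 3: size of the bias, on assumed rates.** Model: logit P(failure) = b0 + b1·(robotic) + b2·(complex), fitted to expected counts. From the protocol: 150 per arm. Assumed: 30% complex (105 simple and 45 complex per arm), the manual failure rates, the true odds ratio (OR), and the share regraded.

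Worked case: manual failure 10% (simple) and 25% (complex), true OR 2.0.
- Robotic failure odds: simple 0.1111 × 2 = 0.2222, so 18.2%; complex 0.3333 × 2 = 0.6667, so 40%.
- Manual counts, failure/success: simple 10.5/94.5; complex 11.25/33.75.
- Robotic counts, correctly graded: simple 19.09/85.91; complex 18/27. Adjusted OR 2.0.
- Robotic counts with half the simple lesions upgraded whatever their outcome: simple 9.55/42.95; complex 27.55/69.95.
- Stratum ORs are then 2.0 (simple) and (27.55/69.95)/(11.25/33.75) = 1.18 (complex). The fitted adjusted OR is 1.48. A Mantel-Haenszel check by hand gives (5.73 + 6.53)/(2.86 + 5.52) = 1.46.

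The same calculation over a range (failure OR, robotic vs manual; above 1 is unfavourable to the device):

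| Manual failure, simple/complex | True adjusted OR | All failed simple robotic cases upgraded | Half of all simple robotic cases upgraded |
|---|---|---|---|
| 10%/25% | 2.0 | 1.56 | 1.48 |
| 5%/15% | 2.5 | 2.22 | 1.8 |
| 2%/6% | 4.0 | 3.86 | 2.99 |
| 1%/3% | 5.0 | 4.95 | 3.80 |
| 10%/25% | 1.0 | 0.83 | 0.73 |
| 5%/15% | 1.0 | 0.915 | 0.71 |

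In the first row the Wald z for arm falls from 2.26 to 1.32 (failures only) or 1.22 (half of all). In the third it falls from 2.59 to 2.43 or 1.97.

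**Step 4: unadjusted comparison.** Regrading leaves each arm's total of failures unchanged. In the first row the unadjusted OR is 1.94 under every regrading pattern.

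**The case against.** The strongest reply has five parts.

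- **The variable is not named.** The field that is formally a lesion classification is the AHA/ACC class, scheduled before the PCI starts. Entered on time, it cannot react to a later robotic failure. This stands, and it removes the second route for that field. It does not remove the first, because the arm is already known.
- **Robotic-arm characteristics are recorded before wiring.** Step 3 of the CorPath technique in 7.2.5 places target lesion characteristics ahead of guidewire advancement, and the 7.2.3 heading is a data list, not a strict sequence. This stands as well.
- **The features have definitions.** Appendix A gives angle bands, length cut-offs and calcification criteria, so grading is not free. That limits how far grades can drift, but judgement remains and no independent reading is stated. 7.2.2 names no grader; that it is the operator is an inference, supported by 2.7, where the cardiologist records lesion measurements during the PCI.
- **Manual failures are probably few.** Technical failure largely means unplanned conversion to manual operation, which cannot happen in the manual arm. The lower-rate rows of the table are then the more relevant ones, and regrading of failures alone hardly matters there.
- **Fisher's exact test is untouched.** This is correct, and every failure stays visible in it.

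A reader might infer that robotic failures will be explained away as complex lesions. The documents do not support that. It needs the 7.2.3 fields or a late-entered class, neither of which 8.1 specifies, and its effect is material only if manual failure rates are high.

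**Conclusion.** The concern holds in a limited form. As scheduled, every lesion complexity field follows disclosure of the arm and no blinded reading is stated, so the covariate in the adjusted technical success model can depend on the arm. The adjusted odds ratio can then be biased towards the device, mainly if robotic-arm lesions are graded as more complex by someone who knows the arm. A grader who erred the other way would bias it against the device.

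The size is illustrative only. Across the assumed settings, upgrading half of the simple robotic-arm lesions moves a failure odds ratio of 2.0 to about 1.5, 4.0 to about 3.0, and 1.0 to about 0.7. Regrading failures alone moves 2.0 to 1.56 at manual failure of 10%/25%, but only 4.0 to 3.86 at 2%/6%. These figures rest on an assumed 30% of complex lesions, assumed failure rates and assumed regrading shares; nothing in the protocol shows that regrading will occur. The bias is confined to the adjusted model.

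**What to change.** In 8.1, define lesion complexity as the highest AHA/ACC class among the target lesions, graded on the diagnostic angiogram when anatomical suitability is confirmed and locked in the EDC before the allocation is released. Move that item out of 7.2.2 accordingly. Use the 7.2.3 characteristics only descriptively, and present the unadjusted comparison alongside the adjusted one.

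The cost is one EDC rule and a short change to 8.1 and 7.2.2. Little extra work is needed, because 4.1, 4.2 and 5.3 already require the anatomy to be judged suitable before randomisation. The downside is in ad-hoc cases, where the allocation can be released only after the diagnostic angiogram has been graded, in the same session. If that is impractical, a reading of the pre-treatment images by someone blind to arm and outcome serves the same purpose; 10.2 already foresees that de-identified angiograms may be collected. Grades already given with the arm known cannot be corrected by changing the timing, so any participants already treated would need the blinded reading.

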| **Other Measures/Procedural Characteristics:** | **Overall Procedure Time**  Defined as the time measured from the insertion of the hemostasis sheath until the removal of the guide catheter.  **PCI Procedure Time -** Defined as the time measured from the insertion of the guide catheter until the removal of the guide catheter.  **Fluoroscopy Time –** total fluoroscopy utilized during the procedure as recorded by an Imaging System.  **Participant Radiation Exposure** – DAP (dose-area-product) and cumulative dose/air kerma as recorded during the procedure.  **Staff Radiation Exposure** – DAP (dose-area-product) and cumulative dose/air kerma as recorded during the procedure.  **Contrast Fluid Volume in mLs**  **Equipment utilization**  **Operator and staff survey of workload**  **Measurement of Lesion and Stented Segment Length**  Compare (1):   - Visual estimate of segment to be stented by clinical operator prior to delivery of PCI device(s). - CorPath GRX System measurement of the segment planned for treatment with stent. |
|  | Compare (2):   - CorPath GRX System measurement of stent length with known length of stented segment |
|  |  |
| **Participant Population:** | Participants aged 18-85 years with evidence of coronary artery disease and with a clinical indication for PCI will be asked to participate in this study. Planned recruitment of 150 participants per study arm over 3 years. |
|  |  |
| **Inclusion Criteria:** | In order to be eligible to participate in this study the individual must meet all of the following criteria:   1. Age ≥18 years- 85 years 2. Participants with coronary artery disease with clinical indication for PCI 3. Participant deemed appropriate for robotic-assisted PCI 4. Provided a signed and dated informed consent form. |
|  |  |
| **Exclusion Criteria:** | An individual who meets any of the following criteria will be excluded from participation in this study:   1. The investigator determines that the participant or the coronary anatomy is not suitable for robotic-assisted PCI. |
|  |  |
| **Investigational Sites:** | Participants will be enrolled from South Western Sydney Local health District and referred to Liverpool Hospital for the PCI procedure. |
|  |  |
|  |  |
| **Principal Investigator:** | [name], D Med Sc, FRACP FACC  Director of Medicine/Interventional Cardiologist  Liverpool Hospital, NSW Australia University of NSW, Sydney |
|  |  |

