### Participant and Staff Radiation Exposure

DAP (dose-area-product) and cumulative dose/air kerma, as recorded during the PCI procedure. Radiation exposure to the patient and staff will be measured by personal dosimeters (Polimaster PM1610) placed at the left shoulder.

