## **Workload assessment survey**

The operator, assistant and nurse involved with the PCI procedure will be asked to complete a survey at the end of the procedure to record an assessment of their workload. This will be via the NASA Task Load Index, which is a survey which assesses workload over 6 domains (mental, physical and temporal demand) [30]. Initially designed for the aerospace industry and NASA, it has been widely utilised and validated across multiple industries [31], including the medical field. It is the most widely cited survey based workload measure [32]

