# Study Design

## **Overview**

This is a randomized controlled trial of the CorPath GRX System versus standard PCI to compare participant outcomes at 72 hours post-procedure or hospital discharge, day 30 and 1 year.

The study population will consist of all consecutive participants undergoing PCI at Liverpool Hospital being asked to provide written informed consent prior to PCI and meet the eligibility criteria.

The study will randomize 300 participants equally into the 2 arms:

- Arm 1: PCI using the CorPath GRX System
- Arm 2: PCI using standard care

All enrolled participants will be followed post procedure through hospital discharge or 72 hours, whichever occurs first. The follow up will occur at day 30 and 1 year post-procedure

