## **Device Training**

The Robotic PCI will only be performed by qualified investigators familiar with the CorPath^®^ GRX System. Training on the CorPath^®^ GRX System and procedure will be performed and documented for the site Investigator who is responsible for using the device.

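### The default independent t-test in Section 8.1 does not fit the workload scores, which come from up to three staff per procedure and very likely from the same staff over many procedures

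*Protocol*

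**What the plan says.** On workload, Section 2.8 states: "The operator, assistant and nurse involved with the PCI procedure will be asked to complete a survey at the end of the procedure". On the instrument it adds: "This will be via the NASA Task Load Index". One randomised participant can therefore yield three scores.

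On numbers and setting, Section 3.1 states: "The study will randomize 300 participants equally into the 2 arms". The protocol summary has participants "referred to Liverpool Hospital for the PCI procedure", so there is one catheterisation service.

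On who operates, Section 9.2 states: "The Robotic PCI will only be performed by qualified investigators familiar with the CorPath" system. Section 7.2.4 sets no comparable condition for standard cases.

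On analysis, Section 8.1 gives Fisher's exact test and logistic regression for technical success, ANOVA for patient radiation and a two-level model for clinical success, because a participant can have several lesions. Its catch-all for the other secondary outcomes reads: "continuous outcomes will be measured using independent t-test (or non-parametric alternative depending on distributional assumptions". Multilevel models are kept for outcomes that are repeated in time.

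On data capture, Section 7.2.2 records details of the operator and the assistant, but not the nurse. Section 7.2.3 lists only "Operator survey of task load". For staff dose, Section 2.6.5 says: "Radiation exposure to the patient and staff will be measured by personal dosimeters (Polimaster PM1610) placed at the left shoulder". It does not say how many staff wear one.

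**The concern.** An independent t-test assumes that each score carries its own information. Workload scores can break this in two ways. Three people scoring the same procedure share its difficulty, so their scores are correlated. A staff member who tends to score high or low takes that habit into every procedure that he or she attends. The non-parametric alternative does not help: it is chosen on distributional grounds and also assumes independence.

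Neither clustering provision in Section 8.1 reaches this. Three raters scoring one procedure at one moment are not a repeat in time, and neither is one nurse scoring different patients.

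Workload is one of the trial's few outcomes about benefit to staff. Double counting of procedures, or a different mix of staff in the two arms, could produce a p-value below 0.05 that does not reflect the device. The opposite error is also possible: removable rater variance could hide a real difference. Part of the problem cannot be repaired later, because rater identity that is not recorded at the procedure is lost to any subsequent analysis plan.

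**Working it through.** **The plan's own figure.** The protocol computes power only for patient radiation (Section 8.1). A 20% reduction of 1284 mGy is 256.8 mGy. The pooled SD is sqrt((180² + 142.83²)/2) = 162.48. With 150 per arm the standard error is 162.48 × sqrt(2/150) = 18.76, and 256.8/18.76 = 13.7, so power is practically 100%. The stated figure of more than 99% reproduces. It does not involve workload, for which no power is given.

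**Inputs for workload.** From the protocol: 3 raters per procedure, 300 procedures in two equal arms, and two-sided 5%. This gives up to 3 × 300 = 900 scores. Assumed, because the protocol gives no values: within-procedure intraclass correlation (ICC) 0.1 to 0.5, staff ICC 0.1 to 0.5, and 6 or 10 staff in a role.

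**Reading A: the three scores are pooled.** The design effect is DE = 1 + (3 − 1) × ICC. The true type I error of a nominal 5% test is 2 × (1 − Φ(1.96/√DE)).

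| ICC | DE | true SE / t-test SE | type I error | effective number (900/DE) |
|---|---|---|---|---|
| 0.1 | 1.2 | 1.10 | 7.4% | 750 |
| 0.3 | 1.6 | 1.26 | 12.1% | 562 |
| 0.5 | 2.0 | 1.41 | 16.6% | 450 |

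If roles differ in mean score, that spread enlarges the t-test's SD but cancels in the arm difference. With role means 0.5 SD apart (assumed), the added variance is (0.25 + 0 + 0.25)/3 = 0.167, and DE is replaced by DE/1.167. The error becomes 5.3%, 9.4% and 13.4% at the same three ICCs.

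**Reading B: one role at a time, one score per procedure.** The within-procedure cluster disappears and staff recurrence remains. The t-test was simulated with 150 procedures per arm, 6 or 10 staff, staff ICC 0.1, 0.3 and 0.5, and 4000 runs per scenario:

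| how staff fall over the arms | type I error |
|---|---|
| assigned independently of arm | 4.5% to 5.6% |
| exactly balanced over arms | 0.8% to 3.7% (true SE 0.73 to 0.95 of the t-test SE) |
| half of the staff do robotic cases, all do standard cases | 14% to 49% |

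A hand check of the third row, for 6 staff and ICC 0.3:
- The t-test variance is (2 × 0.7 + 0.3 × 2/3 + 0.3 × 5/6)/150 = 1.85/150 = 0.0123.
- The mean of 3 staff minus the mean of all 6 adds 0.3/6 = 0.05, so the true variance is 0.0623.
- The SE ratio is sqrt(0.0623/0.0123) = 2.25, and the error is 2 × (1 − Φ(1.96/2.25)) = 38%. The simulation gave 37%.

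One further case: 6 staff assigned independently of arm, staff ICC 0.3, and the device effect itself varying between staff (assumed variance 0.05 or 0.10). The t-test error is then 12% and 19%.

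**The case against.** The strongest reply is that the protocol never says the scores are pooled. One test per role, or one mean per procedure, gives one value per randomised participant, and with staff spread independently of arm the by-role test holds its 5%. This stands. A reader might infer that the trial will treat 900 scores as independent, or that its workload p-values are bound to be too small. The text supports neither: no unit of analysis is stated, and the error can go in either direction.

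A reader might also take Section 9.2 to mean that few operators do the robotic cases, and so expect error rates of a third or more. The section gives no number of operators, and no section says that standard cases are done by a wider group. Those rates show what could happen under assumed staffing. They are not a forecast.

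It is also fair that workload is listed outside any outcome labelled secondary, so it reaches the t-test only through the catch-all clause. Details of operator and assistant are already collected. For staff dose, the number of wearers is not given, so the same structure there is only conditional.

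The reply that all this belongs in a statistical analysis plan is only partly right. Section 8.1 already fixes a default test, and its clustering provisions miss the raters. The nurse's identity must be captured at the procedure. Sections 2.8 and 7.2.3 also disagree on who is surveyed.

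**Conclusion.** The point holds in a conditional form. The default test in Section 8.1 does not suit scores given by several staff per procedure and, very likely, by the same staff across procedures. That staff recur is an inference from 300 procedures at one hospital.

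- If the scores are pooled, the true error is about 7% to 17% for assumed ICCs of 0.1 to 0.5, and lower if roles differ in mean score.
- If each role is tested separately, the test is near nominal or conservative, with lost precision, when staff are spread evenly over the arms. It is anti-conservative if the robotic operators are a narrower group. The size cannot be fixed without staff numbers and ICCs, which the protocol does not give.

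Workload does not set the sample size, so the 300 participants and the patient-radiation power are untouched. The change is worth making because it is cheap and part of it cannot be made after the data are collected.

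**What to change.** 1. In Section 8.1, take workload out of the t-test rule. Name a linear mixed model with arm, role and arm-by-role as fixed effects and random intercepts for procedure and staff member. Report the arm difference for operator, assistant and nurse separately.
2. Add a sensitivity analysis in which the arm effect may vary by staff member, since random intercepts alone do not cover that case.
3. Apply the same model to staff dose if more than one staff member is metered per procedure.
4. Record a coded ID for each survey respondent and dosimeter wearer, adding the nurse to the details already collected under Section 7.2.2.
5. Reconcile Section 7.2.3 with Section 2.8 so that all three surveys are listed.

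Staff adjustment depends on some staff working in both arms, so the number of procedures per staff member and arm should be tabulated beside the result. The cost is slightly more analysis work and one form field, with no extra participants or procedures.
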